### Trial design

INTERPRET-PSY is a mixed method, explanatory sequential (QUANT qual), 3-arm pilot randomized controlled trial (RCT) being conducted in preparation for a subsequent, fully powered RCT evaluating the efficacy of interpreting methods to deliver psycho-oncology care. A timeline of the INTERPRET-PSY project is presented in Fig. 2. This open-label, parallel-group RCT aims to enroll 45 Mandarin-speaking patients with LEP. Participants will be registered by the Memorial Sloan Kettering Cancer Center (MSK) institution-wide, central Protocol Participant Registration system and randomized (using the Clinical Research Database) with equal probability to the RSMI, RCMI, or bilingual provider group and will complete self-report measures (*n* = 15 in each group). As this is a pilot study and not a fully powered RCT, the sample size was determined based on resource considerations and a sample size calculation for the primary outcome of RSMI/RCMI feasibility (see Data analysis plan below) [29]. A purposively sampled subset of participants (i.e., high- and non-responders) in each arm (*n*~6 per arm, pending saturation) and their interpreters and interventionists will be followed up for qualitative data collection in semi-structured interviews to contextualize outcomes and identify barriers and facilitators to interpreter-mediated psycho-oncology counseling.

**Fig. 2 Fig2:**
[figure not shown]
INTERPRET-PSY Pilot RCT Timeline

### Location and participants

The study will take place at MSK in New York City. Research assistants will screen potential patients from MSK and self-referring patients via community providers and consent them as research participants following approval from their primary oncologists. Additionally, a subset of purposively sampled participants as well as their interpreters and interventionists will be consulted through exit interviews to identify barriers and facilitators to successful delivery of MCP-Ch via remote interpreting. All research participants will be compensated to promote retention and complete follow-up. Patients will receive compensation of $50 following completion of each assessment and exit interview. Purposively sampled participants who complete the T3 assessment, their interpreters, and interventionists will receive $50 following completion of the semi-structured interview.

### Eligibility criteria

Inclusion criteria:Speaks English less than “very well” (i.e., has limited English proficiency)Prefers to speak in Mandarin Chinese ≥18 years of ageof Chinese descentDiagnosis of stage III or IV cancer (or roughly equivalent for non-solid tumor cancers)Resides in New York or New Jersey (where the PI is licensed)

Exclusion criteria:Unable/unwilling to use the Zoom platform for telehealth delivery and remote interpretation (*Note*: Participants without an Internet-enabled device will be given or loaned one, and research staff will be available to assist with accessing, downloading, and troubleshooting Zoom if needed).Diagnosed with a primary brain tumorCurrently undergoing hematopoietic stem cell transplantation (HSCT)Major cognitive impairment that would preclude study participation

## Interventions

### RSMI, RCMI, or bilingual provider

Participants assigned to the (1) RSMI, (2) RCMI, and (3) bilingual provider arms (*n* = 15 per arm) will receive all 6 counseling sessions (for details on these sessions, see below) via an English-speaking interventionist and a RSMI interpreter (i.e., a trained bilingual Mandarin-English interpreter who provides remote interpretation within milliseconds of the original speech, nearly simultaneously, almost like a voiceover); an English-speaking interventionist and a RCMI interpreter (i.e., a trained bilingual Mandarin-English interpreter who provides remote consecutive interpretation—by listening as the primary speaker speaks and interpreting only once the primary speaker has finished); and a bilingual interventionist in Mandarin, respectively. Sessions for all 3 arms will take place using a videoconferencing platform and will be recorded. To promote adherence and retention, participants will receive session reminders 1 week, 3 days, and the day prior to the appointment by phone, text, and/or email (with a link to the videoconferencing platform); participants who cannot attend will be given an option to reschedule. Mandarin-English interpreters will be certified as having native bilingual fluency (speaking, understanding, reading, and writing) and meet performance standards for both consecutive and simultaneous interpreting, since they will serve as both RSMI and RCMI interpreters. They will receive intensive training on professional standards of practice and ethics, medical terminology, and linguistic/cultural responsiveness, and will be required to meet professional interpreter standards before study interpreting.

### Description of counseling sessions

The six counseling sessions will utilize the Meaning-in-life Counseling Program for Chinese cancer patients (MCP-Ch) [30], a cultural and linguistic adaptation [30–32] of Meaning-Centered Psychotherapy (MCP). Meaning-Centered Psychotherapy (MCP) is a brief, structured, manualized intervention grounded in the work of Viktor Frankl [33]. MCP has demonstrated efficacy in enhancing advanced cancer patients’ sense of meaning-in-life and QOL while decreasing feelings of depression, anxiety, desire for hastened death, and distress in several randomized controlled trials [34–36]; for a conceptual framework of MCP, see Breitbart, 2016 [37]. MCP guides patients on how to access “sources of meaning” during challenging times: (1) historical (significant memories, relationships, and traditions and their impact on one’s sense of meaning), (2) attitudinal (confronting limitations imposed by cancer), (3) creative (engaging in life through one’s pursuits, including work, hobbies, life roles), and (4) experiential (connecting with life through experiences with love, beauty, humor, etc.).

MCP-Ch consists of six 60-min individual sessions delivered over the span of 3–12 weeks, depending on participant availability. Adaptations to MCP for the Chinese population focused on changing content and strategies to reflect the Chinese cultural context (Table 1) [30, 38]. MCP-Ch will be delivered by doctoral student clinician interventionists who will receive intensive training prior to delivering the intervention and regular supervision after each session.

**Table 1 Tab1:** MCP-Ch overview and adaptations

1	Intro to MCP-Ch	Added additional orientation about psychotherapy and addressed confidentiality concerns among undocumented patients; created handouts with MCP-Ch structure and educational information/FAQ to address cancer myths, cancer stigma, and low health literacy
2	Who Am I? Before Cancer and Now	Given Chinese collectivistic cultural values, clarified that one’s identity includes relationships, beliefs, values
3	Your Life Story: Past, Present, and Future	Given death taboo in Chinese culture, replaced “legacy” with “how you wish to be remembered”; added a list of culturally appropriate questions to guide patients in sharing their life story with others
4	Your Attitude toward Life Challenges	Given death taboo and family-centered model of care in China, made question on “What is a good death” optional based on pt’s prognostic awareness and openness to end-of-life discussion
5	Meaning through Living Your Life	Combined 2 sessions into 1 to improve acceptability & comprehension; revised exercise with culturally syntonic examples of love, beauty, and humor
6	Transitions	No major changes based on stakeholder feedback
All sessions		
Used plain language for manual content and exercises, used “think aloud” technique for MCP definitions, and renamed to “Meaning-in-Life Counseling Program” to counter mental health stigma		

### Assignment of interventions

Participants will be registered by the MSK institution-wide, central Protocol Participant Registration system and randomized (using the Clinical Research Database) to receive MCP-Ch with equal probability via (1) an English-speaking interventionist and an RSMI interpreter; (2) an English-speaking interventionist and an RCMI interpreter; or (3) a bilingual Mandarin-speaking interventionist (no interpreter). Research assistants will randomize a participant following the participant’s completion of the consent, eligibility screener, and baseline assessment. Because a PI ([name]) will be conducting supervision for the interventionists, and because different assessments will be administered depending on the intervention assignment (e.g., clinically significant interpreting errors will be assessed only in the RCMI and RSMI arms), the only person completely blinded to group assignment will be the data analyst/statistician.

## Outcomes

The first goal of INTERPRET-PSY is to determine the feasibility of using RSMI and RCMI to deliver a manualized, culturally adapted counseling intervention to LEP cancer patients. Participants will be deemed not evaluable for feasibility if they drop out prior to Session 6 due to non-intervention related issues (e.g., progression of cancer or death). These non-evaluable participants will be replaced and reasons for dropout tracked. A determination of feasibility for RSMI/RCMI (*primary outcome*) will be met if *n* = 11 complete treatment (a comparable 67% MCP completion rate was achieved in [name] original MCP trial [35]), defined as completing 5 out of 6 sessions (i.e., ≥11 out of 15 participants completing ≥5/6 sessions). We will also calculate the observed recruitment rate, retention rate, participant satisfaction with treatment protocol (*secondary outcome*, scored by calculating the percentage of positive “agree” responses on a satisfaction survey), and telehealth usability in all 3 arms (RSMI, RCMI, bilingual provider). These outcomes will be measured quantitatively within 1 month following the intervention (T8) through a post-intervention assessment.INTERPRET-PSY also will assess the effect of interpreter-mediated delivery on counseling/psychotherapy process outcomes. This will be measured by comparing the RSMI and RCMI groups to the “gold standard” bilingual provider group at post-intervention assessment (T8), administered within 1 month following the intervention. Outcomes will include therapeutic alliance, MCP-Ch content comprehension, and the number and nature of clinically significant interpreting errors in MCP-Ch Session 1 (*secondary outcomes*); participants’ treatment expectancy, post MCP-Ch session 1 (T2); and distress, spiritual well-being, quality of life, anxiety and depression, meaning in life, and hopelessness (*exploratory outcomes*). We will also assess post-session ratings after each MCP-Ch session (T2, T3, T4, T5, T6, and T7).We will identify barriers and facilitators to successful interpreter-mediated delivery of MCP-Ch in semi-structured interviews with “extreme responders” in each of the 3 arms (i.e., participants who score especially high or low on therapeutic alliance, MCP-Ch comprehension, and/or acceptability). These will be assessed approximately 3 months post-intervention (T9).

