**Methods:**

A total of 45 participants will be randomly assigned to one of 3 arms (*n* = 15 RCMI, *n* = 15 RSMI, and *n* = 15 bilingual provider) to receive 6 counseling/psychotherapy sessions. Feasibility and acceptability of the interpreting modalities (RCMI, RSMI) will be evaluated through self-report assessments. Secondary outcomes will include therapeutic alliance, MCP-Ch content comprehension, and clinically significant interpreting errors across the interpreting (RCMI, RSMI) arms. Semi-structured interviews with a purposively sampled subset of patients, their interventionists, and interpreters (if applicable) across all 3 arms will assess potential barriers and facilitators to successful interpreter-mediated communication and outcomes.

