## Measures

A description of each quantitative measure used at each assessment is provided in Table 2, and a timeline of assessments is provided in Table 3. Most measures have demonstrated good reliability and validity in Mandarin-speaking populations (Table 2). Surveys that do not have validated Chinese translations will be translated and checked for quality by qualified translators using an established five-step process for translation and evaluation developed by Forsyth et al. [39]. All measures will be administered either by phone or videoconference by trained bilingual research staff and entered into REDCap, a secure web platform for electronic data capture.

**Table 2 Tab2:** List of assessments

Measure Title	Time Points Used	Outcome	Description of Measure
Demographic and Clinical Characteristics	T1 (Baseline)	n/a	Age (years), gender, race, ethnicity, education, preferred language, level of English proficiency, country of origin, immigration length, frequency of revisiting birthplace, employment status, household income, marital status, household size, religious/spiritual beliefs, health insurance status, most recent cancer diagnosis, and current cancer treatment received
Digital Health Care Literacy (DHCL) [40]	T1 (Baseline)	n/a	The DHCL is a brief (3-item), face valid measure of one’s confidence in the ability to use technological programs or services and the ability to independently troubleshoot technical issues. Cronbach’s α = 0.90 [36]
Feasibility	T8 (Post-intervention)	Primary	Feasibility will be assessed via attendance logs and defined as ≥11 out of 15 participants completing ≥5/6 sessions
Acceptability	T8 (Post-intervention)	Secondary	A 20-item, investigator-initiated, face-valid survey to assess participants’ satisfaction with the intervention, mode of delivery (via RSMI or bilingual interventionist) and effects of treatment (i.e., whether the intervention was helpful). Acceptability will be scored by calculating the percentage of positive (“agree”) responses
Therapeutic Alliance (WAI-S) [41]	T2, T3, T4, T5, T6, T7 (Post-sessions 1–6)	Secondary	The Working Alliance Inventory-Short Form (WAI-S) is a 12-item self-report scale of therapeutic alliance with 2 forms: one for the client, and one for the interventionist. Cronbach’s α = 0.86. [42]*

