### Data analysis plan (by objective)

Counseling completion rates will be calculated; we will treat each interpreting arm (RSMI, RCMI) as a single stage design and will assess each separately for feasibility (*primary outcome*). We will calculate frequencies and percentages to summarize recruitment, randomization, retention, acceptability (*secondary outcome*), and usability across all 3 arms (RSMI, RCMI, and bilingual provider). Based on the calculation outlined by Khan, Sarker, and Hackshaw [58], observing 11 or more successes out of 15 in a given arm would allow us to be sufficiently confident that the population feasibility of the corresponding interpretation mode is 90% against a null of 40%. In our calculations, we have set our statistical power to 90% and our Type I error rate to 0.025 to reduce the chance of false discovery. This provides us with sufficient combined statistical power, assuming the two tests are independent.We will summarize (1) therapeutic alliance scores and MCP-Ch content comprehension at T4 across all 3 arms (RSMI, RCMI, and bilingual provider) and (2) number and nature of clinically significant interpreting errors in MCP-Ch Session 1 across the interpreting arms (RSMI, RCMI) (*secondary outcomes*). We will also summarize treatment credibility/expectancy at T2 and differences in post- vs. pre-intervention distress, spiritual well-being, quality of life, anxiety and depression, meaning-in-life, hopelessness by arm (*exploratory outcomes*). These descriptive summaries by arm will provide preliminary indications of whether delivery of psycho-oncology counseling via RSMI or RCMI may potentially achieve clinically significant benefits, which will aid in the design of, and be further assessed in, a subsequent fully powered trial [29]. We will assess baseline contextual factors at T1 (e.g., digital health care literacy, level of English proficiency) to examine whether therapeutic alliance and MCP-Ch content comprehension scores differ by these variables. We will use an error analysis tool developed by Gany et al. [21] to obtain the number and nature of clinically significant errors in MCP-Ch Session 1. Specifically, a panel of 2–4 psycho-oncology clinicians blinded to the interpreting method (i.e., RSMI or RCMI) will review and code transcripts. They will independently code each script to identify clinically significant content and meet to reconcile any differences in their selection of clinically significant content. Examples of potentially clinically significant content include history of cancer diagnosis, past psychiatric history, MCP-Ch session exercises, and plans for future visits. Once all clinically significant content has been identified, a second blinded panel of 2–4 bilingual coders will independently code clinically significant content to identify interpreting errors, yielding a total count of clinically significant interpreting errors. To ensure rigor, coders on both panels will first separately conduct preliminary analyses on a subset of transcripts using the described protocol. Interrater reliability will be assessed by calculating percent agreement. Consensus meetings will be held to adjudicate disagreements and refine error categories and the analytic approach as needed until strong interrater reliability is reached (i.e., *k* = 0.80), at which point coders will commence coding of the remaining transcripts.To assess our semi-structured interviews with “extreme responders,” we will use thematic content analysis [59] to derive insights directly from participants’ narratives, following established guidelines for conducting rigorous qualitative research [60]. First, coders will each read a subset of interviews and develop codes to characterize responses. Coders will then meet to establish an initial codebook, which will be used to code the remaining interviews. Regular consensus meetings will be held to confirm the reliability of coding. The codebook will be iteratively revised as new codes emerge, and codes will be summarized into themes. Prominent themes will include those observed across the majority of interviews as well as key divergences between sub-groups. Findings will be integrated using NVivo [61], which enables qualitative and quantitative data to be paired by participant and in summary format. The coded qualitative data will be explored in relationship to participant outcomes, baseline characteristics, contextual factors, and study arm to further elucidate barriers and facilitators to the implementation of remote interpreting in the psycho-oncology setting.

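### The not-evaluable rule discards participants who have already met the five-session success definition, and replacing the other illness dropouts makes 11/15 a count among those who stayed well enough to finish

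*Protocol article*

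**What the plan says.** All references are to the protocol article.

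- **Outcomes, exclusion:** "Participants will be deemed not evaluable for feasibility if they drop out prior to Session 6 due to non-intervention related issues", with progression and death as examples. Then: "These non-evaluable participants will be replaced and reasons for dropout tracked".
- **Outcomes, success:** completing treatment is "defined as completing 5 out of 6 sessions (i.e., ≥11 out of 15 participants completing ≥5/6 sessions". Key study objectives uses the same threshold, as does Table 2 under Measures: "Feasibility will be assessed via attendance logs and defined as ≥11 out of 15 participants completing ≥5/6 sessions".
- **Data analysis plan:** "we will treat each interpreting arm (RSMI, RCMI) as a single stage design and will assess each separately for feasibility". Observing 11 of 15 is meant to support a claim about "population feasibility of the corresponding interpretation mode is 90% against a null of 40" per cent, and "we have set our statistical power to 90% and our Type I error rate to 0.025".
- **Discussion:** the same count drives progression: go at 11 or more of 15, amend at 7 to 10, stop at 6 or fewer.
- **Sample size:** the Abstract states "A total of 45 participants will be randomly assigned to one of 3 arms". Trial design gives 45 as the number the trial aims to enrol.

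Neither the Data analysis plan nor the Discussion mentions the exclusion when it applies the 11/15 rule. Participants have stage III or IV disease (Eligibility criteria), and the six sessions run over 3 to 12 weeks (Description of counseling sessions).

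**The concern.** There are two separate problems.

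First, the exclusion point and the success point do not match. Success is reached at five sessions, but a participant can still be declared not evaluable up to Session 6. Whoever stops between the two for illness is a success under one sentence and is deleted and replaced under another. An analyst following the text cannot classify that person.

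Second, the primary outcome is completion, and the rule removes some non-completers after randomisation. The surviving count describes completion among those who did not leave for illness. The Data analysis plan nonetheless presents it as the population feasibility of the interpreting mode, and it feeds the go/amend/stop decision for a later trial that will have to plan for everyone it randomises. With advanced cancer, illness dropout during treatment is foreseeable, and the rule itself names it.

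**Working it through.** **Reproducing the plan's figure.** Inputs from the Data analysis plan: n = 15, cut-off 11, null 0.40, target 0.90, type I error 0.025, power 90%. By exact binomial:

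- P(X ≥ 11 | 15, 0.40) = 0.0093
- P(X ≥ 10 | 15, 0.40) = 0.034, above 0.025
- P(X ≥ 11 | 15, 0.90) = 0.987

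So 11 is the smallest valid cut-off at n = 15, and the stated error rate and power are met as bounds. The design figure is sound.

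**What the exclusion does to the tested rate.** Let p be completion (five or more sessions) among all randomised, d the share declared not evaluable, and f the share of those who had already attended five sessions. The rate among evaluable participants is

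p_eval = (p − f·d)/(1 − d).

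This exceeds p when f < p and falls below p when f > p. The article gives none of p, d and f.

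**Rule as written (f unknown), with d = 20% assumed:**

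| f | p_eval at p = 0.40 | P(go) | p_eval at p = 0.60 | P(go) |
|---|---|---|---|---|
| 0 | 0.500 | 0.059 | 0.750 | 0.69 |
| 1/6 | 0.458 | 0.030 | 0.708 | 0.54 |
| 1/2 | 0.375 | 0.005 | 0.625 | 0.28 |
| no exclusion | 0.400 | 0.0093 | 0.600 | 0.22 |

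Discarding five-session completers pulls the count down, and removing earlier dropouts pulls it up. The direction is not fixed by the text.

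**With five-session completers kept as successes (f = 0),** p_eval = p/(1 − d), which is above p for any d > 0. Here P(go) = P(X ≥ 11 | 15, p_eval):

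| d (assumed) | p_eval at p = 0.40 | false go | p_eval at p = 0.60 | P(go) |
|---|---|---|---|---|
| 0 | 0.400 | 0.0093 | 0.600 | 0.22 |
| 5% | 0.421 | 0.015 | 0.632 | 0.30 |
| 10% | 0.444 | 0.023 | 0.667 | 0.40 |
| 15% | 0.471 | 0.037 | 0.706 | 0.54 |
| 20% | 0.500 | 0.059 | 0.750 | 0.69 |

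The stated 0.025 is passed somewhere between d = 10% and 15%.

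**One concrete case.** Suppose an arm reaches 11 of 15 evaluable (73%) after replacing three participants who had fewer than five sessions. Completion among those randomised is 11/18 = 61%. For n = 18, P(X ≥ 11 | 18, 0.40) = 0.058 and P(X ≥ 12 | 18, 0.40) = 0.020, so the cut-off is 12. The arm is green on the evaluable count and misses the cut-off on the all-randomised count.

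**The case against.** The strongest reply is that the stated objective is feasibility of the interpreting modes. All arms receive the same counselling and differ in how language is handled, so death or progression says little about whether simultaneous or consecutive interpreting works. Excluding such dropouts is prespecified and openly stated, their reasons are tracked, and recruitment, randomization and retention are summarised for all three arms. This stands in part. Completion among those not leaving for illness is a legitimate target, and changing the primary denominator is a choice of target more than the correction of an error. But the article does not state that target, and the reply does not touch the five-session contradiction.

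Three stronger readings are tempting and are not supported:

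- *A reader might infer that the rule as written is biased towards feasible.* That holds only if f is below p, and the documents do not give f.
- *A reader might infer that the stated type I error fails.* With f = 0 it holds at d of 5% and 10%. It is exceeded only at higher assumed d.
- *A reader might infer that 45 randomised contradicts replacement, or that a definite larger number is needed.* Because replacement is stated openly and 45 is also described as an enrolment aim, 45 reads naturally as the evaluable target. Any total depends on an assumed d and on which arms replace. At d = 20%, 45/0.80 = 56.25 if all three arms replace, but 15 + 30/0.80 = 52.5 if only the interpreting arms do.

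The article also does not say who judges whether a dropout is related to the intervention. A full protocol may say so, and nothing here rests on it.

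**Conclusion.** The point holds in two parts. The clash between the five-session success definition and the exclusion before Session 6 is an error in the text and needs no assumption. The replacement of the remaining illness dropouts is a badly fixed primary count. Once the first part is repaired, it raises the tested completion rate whenever anyone is removed, and the article reports the result as population feasibility. The size rests on assumed dropout of 5% to 20%: from minor (false go 0.015, within the limit) to more than twice the stated error rate (0.059). At 60% completion the chance of a go goes from 0.22 to between 0.30 and 0.69. The documents do not support the further step that the all-randomised count must replace the evaluable count as primary. They do support reporting both and saying which question each answers.

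**What to change.** 1. Amend Outcomes so that anyone with five or more sessions is a success whatever follows, and so that the not-evaluable rule can apply only to participants with fewer than five.
2. For each interpreting arm, also report from the attendance logs the completion count over all randomised participants, with fewer than five sessions for any reason as non-completion. Test it against 40% with the exact cut-off for the actual n, for example 12/18 (alpha 0.020). That cut-off treats n as fixed, although replacement makes it depend on dropout, so label its alpha as nominal.
3. Require the go/amend/stop decision in the Discussion to be read with this count.
4. If the evaluable-only count stays primary, state that its target is completion among those not leaving for illness.
5. State that 45 is the evaluable target, that the number randomised will exceed it by the number replaced, and which arms replace.

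No new data are needed, but the wording change requires ethics board approval, and enrolment began in March 2024, so it should be settled before the count is made. The all-randomised figure will be less favourable. Power may also fall. If the 90% alternative refers to evaluable participants, completion over all randomised is 0.90 × (1 − d). That is 0.81 at d = 10% and 0.72 at d = 20%, where P(X ≥ 11 of 15) drops from 0.987 to 0.86 and 0.585.
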